## Abstract

**Background:**

Standard treatment for locally advanced rectal cancer includes 5–6 weeks of neoadjuvant chemoradiotherapy (NACRT) followed by total mesorectal excision 6–8 weeks later. NACRT improves local disease control and surgical outcomes but also causes side effects including fatigue, diarrhea, hand-foot syndrome, and physical deconditioning that may impede quality of life (QoL), treatment completion, treatment response, and long-term prognosis. Interventions to improve treatment outcomes and manage side effects that are safe, tolerable and low-cost are highly desirable. Exercise has been shown to improve some of these outcomes in other cancer patient groups but no study to date has examined the potential benefits (and harms) of exercise training during and after NACRT for rectal cancer.

**Methods/design:**

The Exercise During and After Neoadjuvant Rectal Cancer Treatment (EXERT) trial is a single-center, prospective, two-armed, phase II randomized controlled trial designed to test the preliminary efficacy of exercise training in this clinical setting and to further evaluate its feasibility and safety. Participants will be 60 rectal cancer patients scheduled to receive long-course NACRT followed by total mesorectal excision. Participants will be randomly assigned to exercise training or usual care. Participants in the exercise training group will be asked to complete three supervised, high-intensity interval training sessions/week during NACRT and ≥ 150 min/week of unsupervised, moderate-to-vigorous-intensity, continuous exercise training after NACRT prior to surgery. Participants in the usual care group will be asked not to increase their exercise from baseline. Assessments will be completed pre NACRT, post NACRT, and pre surgery. The primary endpoint will be cardiorespiratory fitness (VO_2_ peak) at the post-NACRT time point assessed by a graded exercise test. Secondary endpoints will include functional fitness assessed by the Senior’s Fitness Test, QoL assessed by the European Organisation of Research and Treatment of Cancer, and symptom management assessed by the M.D. Anderson Symptom Inventory. Exploratory clinical endpoints will include treatment toxicities, treatment completion, treatment response, and surgical complications.

**Discussion:**

If the preliminary findings of EXERT are positive, additional research will be warranted to confirm whether exercise is an innovative treatment to maintain QoL, manage side effects, and/or improve treatment outcomes in rectal cancer patients.

**Trial registration:**

ClinicalTrials.gov, ID: NCT03082495. Registered on 9 February, 2017.

**Electronic supplementary material:**

The online version of this article (doi:10.1186/s13063-017-2398-1) contains supplementary material, which is available to authorized users.

## Background

Current standard treatment for locally advanced rectal cancer (stages II and III) includes long-course (5–6 weeks) neoadjuvant chemoradiotherapy (NACRT) followed by surgical resection using total mesorectal excision 6–8 weeks later [1]. When compared to postoperative chemoradiotherapy, NACRT improves local recurrences rates and may improve surgical outcomes in some patients [2, 3]. Unfortunately, NACRT causes acute toxicities including fatigue, diarrhea, hand-foot syndrome, hematologic toxicity, cardiotoxicity, and physical deconditioning that can cause declines in quality of life (QoL) [4] and may even impede treatment completion, treatment response, and long-term prognosis. Safe, tolerable, and low-cost interventions to manage these side effects and improve treatment outcomes in this clinical setting are highly desirable. We propose that an exercise training intervention initiated during NACRT in patients with rectal cancer may improve cardiorespiratory fitness, symptom management, QoL, treatment completion, treatment response, surgical complications, and possibly even survival (Fig. 1).

**Fig. 1 Fig1:**
[figure not shown]
Proposed effects of exercise during and after neoadjuvant chemoradiotherapy in rectal cancer patients

Exercise has been shown to manage some side effects and improve QoL in several cancer patient groups receiving adjuvant therapy [5]. Moreover, limited research has suggested that exercise during chemotherapy for some cancer patient groups may improve chemotherapy completion rates [6–8], treatment response [9], and even long-term survival [10]. Additionally, there is some evidence that pre-operative exercise may improve fitness and surgical outcomes in cancer patients [11]. Finally, preliminary evidence has suggested that exercise is feasible and safe in the neoadjuvant setting [12].

Despite the emerging evidence for the benefits of exercise in some cancer patient groups receiving some treatment protocols, only preliminary research has examined exercise in rectal cancer patients during and after NACRT. Similar to drug trials, exercise trials have demonstrated that research in one cancer patient/treatment group rarely generalizes to another cancer patient/treatment group [13]. Preliminary research suggests that exercise initiated immediately *after* NACRT is feasible and may improve cardiorespiratory fitness [14], which has prompted a phase II trial in this clinical space [15]. Furthermore, two phase I studies [16, 17], including one from our group [16], have demonstrated the preliminary feasibility and safety of exercise *during* NACRT for rectal cancer patients. Finally, one ongoing randomized controlled trial is examining the feasibility of an unsupervised walking program both during and after NACRT (ISRCTN62859294). Here, we propose the Exercise During and After Neoadjuvant Rectal Cancer Treatment (EXERT) trial which, to our knowledge, is the first phase II trial designed to examine the preliminary efficacy of exercise training in rectal cancer patients during and after NACRT.

### Study objectives

#### Primary objective

The primary objective of the EXERT trial is to examine the effects of a supervised, high-intensity interval training (HIIT) program, compared to usual care, on cardiorespiratory fitness during NACRT.

#### Secondary objectives

The secondary objectives of the EXERT trial are to (1) compare an unsupervised, moderate-to-vigorous-intensity, continuous exercise training program after NACRT to usual care on cardiorespiratory fitness, (2) compare the supervised HIIT program during NACRT and unsupervised continuous exercise training program after NACRT on functional fitness, QoL, and symptom burden, (3) establish the feasibility and safety of the supervised HIIT program during NACRT, and (4) investigate the motivational outcomes and determinants of exercise during and after NACRT.

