#### Exploratory objectives

The exploratory objectives of the EXERT trial are to compare a supervised HIIT program during NACRT followed by an unsupervised, moderate-to-vigorous-intensity, continuous exercise training program after NACRT to usual care on clinical outcomes including treatment toxicities, treatment completion, treatment response, and surgical complications.

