## Methods/design

### Study design

The EXERT trial will be a single-center, prospective, two-armed, phase II randomized controlled trial conducted in Edmonton, Alberta. The EXERT trial has been approved by the Health Research Ethics Board of Alberta-Cancer Committee and all participants will be required to provide written informed consent. The proposed participant flow through the study is shown in Fig. 2. Health-related fitness outcomes and patient-reported outcomes will be assessed at baseline (0–7 days before starting NACRT), post NACRT (0–7 days after completing NACRT), and pre surgery (7–14 days before the planned surgery date). The Standard Protocol Items: Recommendations for Interventional Trials (SPIRIT) Figure for the EXERT trial is shown in Fig. 3 (Additional file 1).

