### Randomization and blinding

After completing all baseline assessments, patients will be randomly assigned to either the exercise training group or usual care group in a 1:1 ratio using block randomization. A research assistant, not otherwise involved in the trial, will generate the block sizes and randomization sequence using a computer-generated random allocation sequence which will be concealed from the recruiting study coordinator. Given the nature of the intervention, it is not possible to blind the investigators or participants to group allocation. Additionally, due to logistical challenges at our facility, it is difficult to blind outcome assessors to group allocation for the primary outcome of cardiorespiratory fitness and the secondary outcomes of functional fitness. Nevertheless, fitness outcome assessors will follow a detailed protocol and be trained in the importance of standardizing outcome assessments and avoiding bias. Moreover, outcome assessors will not review the metabolic data during the cardiorespiratory fitness test, and the criteria for achieving peak volume of oxygen consumption (VO_2_ peak) will undergo an independent review. Finally, outcome assessors will be blinded to group assignment for the exploratory outcomes of treatment toxicities, treatment completion, treatment response, and surgical complications which will be assessed by medical staff not otherwise involved in the study.

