### Intervention

For patients randomized to the exercise training group, the intervention will be divided into two phases: (1) during NACRT and (2) post NACRT. During NACRT, all of the exercise sessions will be supervised by a certified exercise physiologist. We previously determined that it was feasible for patients to attend supervised exercise sessions at our fitness center (within a 5-min walk from the cancer center) since they were already coming to the cancer center 5 days/week for radiation treatment [16]. During NACRT, patients will be asked to complete 18 supervised HIIT sessions (i.e., three sessions/week for 6 weeks) and to continue with any light-to-moderate-intensity exercise that they were performing at baseline. We selected a HIIT program for evaluation because of its ability to maximize cardiorespiratory fitness improvements over a short period of time [18]. Moreover, HIIT has previously demonstrated safety and feasibility in clinical populations including patients with cardiometabolic disease [19], diabetes [20], and during adjuvant chemotherapy in patients with mixed cancers [21]. HIIT is characterized by relatively short bursts of vigorous-intensity exercise, interspersed by periods of rest or light-intensity exercise for recovery. There are an endless number of possible combinations that can make up a HIIT program; however, HIIT typically refers to exercise intensities corresponding to ≥ 85% of peak heart rate or ≥ 80% of VO_2_ peak [19]. We have designed the HIIT program in the EXERT trial to closely match a previously published HIIT program which has demonstrated feasibility, safety, and greater improvements in cardiorespiratory fitness in patients with coronary artery disease [22].

In our phase I study, we demonstrated an excellent median attendance rate of 83% to three sessions/week of moderate-intensity, continuous exercise training during NACRT [16]. Moreover, no adverse events were observed and our evaluation was that even higher-intensity exercise training would be feasible in this clinical setting. Nevertheless, the safety and feasibly of HIIT during NACRT in rectal cancer patients has yet to be established and is a key objective of our study.

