After NACRT, patients will be asked to complete at least 150 min of unsupervised, moderate-to-vigorous-intensity, continuous exercise training training/week (current Canadian Physical Activity Guidelines). In our phase I study, it was feasible for patients to achieve 150 min of mostly unsupervised, moderate-intensity exercise/week after NACRT. Although local patients in our pilot study were offered a supervised exercise program after NACRT, only two out of 16 patients expressed interest in continuing with supervised exercise in this phase and patients mainly achieved their weekly exercise minutes by walking outdoors or by using pre-existing home exercise equipment (e.g., treadmill, elliptical, and upright bike). For this reason, we felt that it would be difficult to deliver a standardized and replicable HIIT program after NACRT. Moreover, in our phase I study, cardiorespiratory fitness improved by 2.4 ml/kg/min from post NACRT to pre surgery suggesting that an unsupervised, moderate-intensity, continuous exercise training program may be effective at improving cardiorespiratory fitness after NACRT and prior to surgery in rectal cancer patients. Finally, after our experience in the phase I study, we felt that it would be feasible and safe for rectal cancer patients to complete moderate-to-vigorous-intensity continuous exercise in this phase and may result in greater improvements in cardiorespiratory fitness. Nevertheless, one of the goals of the EXERT trial is to further establish the feasibility and safety of continuous exercise training after NACRT and to determine its preliminary efficacy at improving outcomes for rectal cancer patients.

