### Data analysis

We will use analysis of covariance (ANCOVA) at both the post-NACRT and pre-surgery time points to compare the two groups on all primary and secondary outcomes with adjustment for baseline value of the outcome as well as other potential covariates. All statistical analyses will be based on the intention-to-treat principle and include all patients with baseline and follow-up data. No missing data replacement strategies will be performed for this phase II trial as we anticipate < 10% missing data. Chi-square analyses will be used to explore between-group differences in the categorical and ordinal clinical outcomes. All analyses will be performed using SPSS (SPSS Inc., Chicago, IL, USA).

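### Secondary objective 1 claims to compare the post-NACRT unsupervised program with usual care, but the pre-surgery contrast estimates HIIT followed by that program

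*Protocol article*

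**What the plan says.** All places are in the protocol article.

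- **Secondary objectives.** Objective 1 is to "compare an unsupervised, moderate-to-vigorous-intensity, continuous exercise training program after NACRT to usual care on cardiorespiratory fitness". Only the second-phase program is named as the treatment.
- **Intervention.** Among the trial's goals for continuous training after NACRT, beside feasibility and safety, is "to determine its preliminary efficacy at improving outcomes for rectal cancer patients".
- **Study design.** The trial is a "single-center, prospective, two-armed, phase II randomized controlled trial conducted in Edmonton, Alberta". Baseline is measured in the week before NACRT begins.
- **Randomization and blinding.** Allocation precedes treatment: "After completing all baseline assessments, patients will be randomly assigned to either the exercise training group or usual care group in a 1:1 ratio". No later randomization is described.
- **Intervention.** For the exercise arm, "the intervention will be divided into two phases: (1) during NACRT and (2) post NACRT". The same patients are assigned both phases, in that order.
- **Data analysis.** The two groups are compared by ANCOVA post NACRT and again pre surgery, "with adjustment for baseline value of the outcome as well as other potential covariates".
- **Exploratory objectives.** Here the contrast is worded for the whole sequence: "compare a supervised HIIT program during NACRT followed by an unsupervised, moderate-to-vigorous-intensity, continuous exercise training program after NACRT to usual care".

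**The concern.** The treatment named in objective 1 is not the treatment that the pre-surgery comparison evaluates. By then the exercise arm has been assigned six weeks of supervised HIIT and then the unsupervised program, while usual care has been assigned neither. A difference between arms may come from HIIT, from the later program, or from both. Adjusting for a value measured before either phase cannot separate them.

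What is at stake is the meaning of a secondary result. The two components differ in supervision, intensity and timing. If the pre-surgery difference is reported in the words of objective 1, a lasting HIIT benefit would count as efficacy of unsupervised training, and a lasting HIIT harm would count against it.

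**Working it through.** **1. The plan's own figure.** The Sample size section gives 30 patients per arm, 10% missing data (27 per arm analyzed), a difference of 3.5 ml/kg/min post NACRT, SD 5.6, two-sided 0.05, covariate adjustment and 80% power. The correlation behind the adjustment is not stated.

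- Unadjusted power with 27 per arm is 63%.
- For 80%, the residual SD must be 3.5 / [(1.960 + 0.842) × √(2/27)] = 4.59.
- That requires a correlation of √[1 − (4.59/5.6)²] = 0.573.

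The 80% is therefore attainable but cannot be confirmed from the article. The present point does not depend on it. I use 3.5 only as a convenient size and 0.573 only as an assumed correlation between visits.

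**2. What each contrast estimates.** Let H be the HIIT effect post NACRT (exercise minus usual care), c the fraction of that difference still present pre surgery, and P the effect of the unsupervised program.

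- Post-NACRT ANCOVA: H.
- Pre-surgery ANCOVA adjusted for the pre-NACRT value: c·H + P.
- Difference between arms in change from post NACRT to pre surgery: (c·H + P) − H = P − (1 − c)·H.

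The trial supplies two between-arm differences for three unknowns. The pre-surgery contrast equals P only if c·H = 0. The change contrast equals P only if (1 − c)·H = 0. No arm receives the second phase alone, so the data cannot show which condition holds, if either.

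**3. Would the post-NACRT value as a covariate help?** The open phrase about other covariates might seem to allow it. That value is measured after randomization and may already have been changed by HIIT. With equal correlation ρ between all visits, the slope on it is ρ/(1 + ρ) = 0.573/1.573 = 0.364. The adjusted contrast is then c·H + P − 0.364·H. With H = 3.5 this is 3.5c + P − 1.27, which in general is not P either.

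**4. Numbers.** Set H = 3.5 and P = 0, so that a correct estimate of the second phase would be zero. The simulated columns come from 6,000 trials per row with 27 per arm, SD 5.6 and correlation 0.573 between all visits.

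| Retained fraction c (assumed) | Pre-surgery contrast, 3.5 × c | Simulated ANCOVA estimate | Significant at 0.05 | Change contrast, −(1 − c) × 3.5 | Simulated estimate with post-NACRT covariate |
|---|---|---|---|---|---|
| 0% | 0 | −0.01 | 5% | −3.50 | −1.27 |
| 25% | 0.875 | 0.87 | 10% | −2.625 | −0.40 |
| 50% | 1.75 | 1.75 | 27% | −1.75 | 0.475 |
| 75% | 2.625 | 2.63 | 54% | −0.875 | 1.35 |
| 100% | 3.50 | 3.53 | 79% | 0 | 2.25 |

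Units are ml/kg/min. A lasting harm from HIIT would reverse the signs.

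**The case against.** **The analysis is sound and the primary endpoint is untouched.** This stands. The post-NACRT comparison is a clean randomized contrast of HIIT with usual care. The pre-surgery ANCOVA is a valid estimate of the two-phase strategy. A reader might infer that the ANCOVA is wrong. It is not; only the label put on its result is.

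**Both time points will be reported.** If HIIT gave 3.5 and nothing were added later, contrasts of 3.5 and 3.5 would show that the gain was already there post NACRT. This reduces the risk of misreading. It does not isolate the second phase, because two equal contrasts also fit a HIIT effect that faded while the later program made up the loss.

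**Full retention may be unlikely.** The Discussion says that in the phase I study most outcomes fell during NACRT and recovered afterwards. If usual-care patients recover too, a carried-over difference would shrink. That study had no control group, so this is suggestive only. It is a reason to show the whole range, including 0%, where nothing is misattributed.

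**The wrong component could go to phase III.** A reader might draw this conclusion, but the article sets no rule for choosing between components and mostly frames its conclusions around exercise during and after NACRT as a package. I do not claim it.

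**Objective 2 plans a head-to-head test of the two programs.** Read literally, it is to "compare the supervised HIIT program during NACRT and unsupervised continuous exercise training program after NACRT on functional fitness, QoL, and symptom burden", and usual care is not mentioned. Since the Data analysis section compares the two arms on all secondary outcomes, the missing comparator is most likely an editorial omission and not a planned comparison of one program with the other.

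**Conclusion.** Objective 1 and the efficacy clause under Intervention are wrong as worded. The design supports a statement about HIIT followed by unsupervised training versus usual care at pre surgery. It supports no randomized statement about the second phase alone, and a separate statistical analysis plan could not supply one without further untestable assumptions.

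The size of any misattribution is unknown. The range of 0 to 3.5 ml/kg/min rests on three assumptions: a HIIT effect equal to the difference the trial is sized to detect (not an effect the protocol says it expects), a zero second-phase effect, and retention anywhere from 0 to 100%. The significance rates also rest on the assumed correlation of 0.573. Misattribution follows only if the result is reported as objective 1 is worded, so it should not be read as certain.

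Severity: should fix. This is a fault in what one secondary objective claims, repeated once, and not in the analysis.

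**What to change.** 1. Reword secondary objective 1 on the model of the exploratory objectives: the effect on cardiorespiratory fitness, at pre surgery, of HIIT during NACRT followed by unsupervised continuous training, compared with usual care.
2. Qualify the preliminary-efficacy clause under Intervention in the same way. Its feasibility and safety goal can stay as it is.
3. If phase-specific information is wanted, show the change from post NACRT to pre surgery by arm, labeled as descriptive and not as a randomized comparison of the second phase.
4. As an editorial correction, name usual care as the comparator in objective 2.

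The cost is wording. Sample size, data collection, the primary endpoint and the planned ANCOVA are unchanged. What is given up is a phase-specific efficacy claim that the design cannot support.

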#### Exploratory objectives

The exploratory objectives of the EXERT trial are to compare a supervised HIIT program during NACRT followed by an unsupervised, moderate-to-vigorous-intensity, continuous exercise training program after NACRT to usual care on clinical outcomes including treatment toxicities, treatment completion, treatment response, and surgical complications.

## Methods/design

### Study design

The EXERT trial will be a single-center, prospective, two-armed, phase II randomized controlled trial conducted in Edmonton, Alberta. The EXERT trial has been approved by the Health Research Ethics Board of Alberta-Cancer Committee and all participants will be required to provide written informed consent. The proposed participant flow through the study is shown in Fig. 2. Health-related fitness outcomes and patient-reported outcomes will be assessed at baseline (0–7 days before starting NACRT), post NACRT (0–7 days after completing NACRT), and pre surgery (7–14 days before the planned surgery date). The Standard Protocol Items: Recommendations for Interventional Trials (SPIRIT) Figure for the EXERT trial is shown in Fig. 3 (Additional file 1).

